## Abstract

**Background:**

Physical inactivity has been deemed a significant, contributing factor to childhood overweight and obesity. In recent years, many school systems removed recess and/or physical education from their curriculum due to growing pressure to increase academic scores. With the vast majority of children’s time spent in school, alternative strategies to re-introduce physical activity back into schools are necessary. A creative yet underutilized solution to engage children in physical activity may be in before-school programs. The objective of the proposed study is to examine the effect of an unstructured, moderate to vigorous, before-school physical activity program on academic performance, classroom behavior, emotions, and other health related measures.

**Methods/Design:**

Children in 3rd–5th grade will participate in a before-school (7:30–8:15 a.m.), physical activity program for 12 weeks, 3 days a week. Children will be able to choose their preferred activity and asked to sustain physical activity of moderate to vigorous intensity with individual heart rate monitored during each session.

**Discussion:**

The proposed study explores an innovative method of engaging and increasing physical activity in children. The results of this study will provide evidence to support the feasibility of an unstructured, moderate to vigorous, before-school physical activity program in children and provide insight regarding the ideal physical activity intensity and duration necessary to achieve a positive increase in academic performance.

**Trial registration:**

ClinicalTrials.gov Identifier: NCT01505244

## Background

The current guidelines for physical activity recommend that children should partake in regular, moderate to vigorous physical activity for 60 minutes or more each day [1]. Not only are children not meeting the recommended amount of physical activity but schools are also contributing to this culture of physical inactivity. In recent years, many school systems removed recess and/or physical education from their curriculum due to growing pressure to increase academic scores [2]. In addition to the importance of physical activity for overall physical health and fitness, classroom behavior, academic skills, and attention may also improve in children with increasing physical activity [3-5]. There appears to be a positive association between physical activity and academic performance and behavior; however, further research to delineate the ideal duration and intensity is warranted particularly in elementary school children [3-5].

With the absence of physical activity during the school day, after-school programs have become a popular option to help children reach the recommended 60 minutes of activity. Unfortunately, children participating in after-school programs only engage in approximately 20 minutes of moderate to vigorous physical activity with most of their time spent in light or sedentary behavior [5]. Modifying the structure of these school programs in order to better regulate the levels of physical activity in children may seem to be an appropriate response; however, when allowed to engage in unstructured “free-play”, children were significantly more likely to achieve physical activity levels considered to be of moderate to vigorous intensity. Trost et al. [5] observed a 24–55% decrease in moderate to vigorous physical activity during an organized activity period compared to the preferable “free-play”.

A creative yet underutilized potential solution to engage children in physical activity may be before-school programs. Only one study to date was identified which examined the effects of a before-school physical activity program on overall physical activity. Mahar et al. [6] observed children that participated in before-school physical activity were significantly more attentive throughout the day. Furthermore, these children did not become more inactive throughout the day when engaged in early activity [6]. The study by Mahar et al. [6] lends credence to the implementation of a before-school physical activity program to help children achieve the recommended 60 minutes of daily activity without taking time away from academics; however much more research is warranted.

With physical inactivity deemed as a significant contributing factor to childhood overweight and obesity and with the vast majority of children’s time spent in school, this may be the ideal location for implementing physical activity interventions [7]. The objective of the proposed study is to examine the effect of an unstructured, moderate to vigorous, before-school physical activity program on academic performance, classroom behavior, emotions, and other health related measures. The proposed study may provide insight to the relationship between physical activity and academic performance as well as assist in the design of future physical activity interventions. Moreover, to the authors’ knowledge, no study has examined the effect of an unstructured, before-school physical activity program. Therefore, the proposed study protocol represents a novel approach to increasing physical activity in children.

## Methods/Design

### Objectives

This study will aim to implement a 12- week before-school, physical activity program and examine the effect of this unstructured, moderate to vigorous, before-school physical activity program on academic performance, classroom behavior, emotions, and other health related measures. This study will take place at Malletts Bay School in Colchester, Vermont (VT), the 3rd largest community in the state of VT. Approval to conduct the study was received from the Colchester School Board as well as from the principal of Malletts Bay School. Malletts Bay is a public school servicing 3rd, 4th, and 5th graders with a total of 447 students (229 males, 218 females). Approximately 35% of these students are eligible and participate in the Free and Reduced Lunch Program. The proposed protocol was approved by the Institutional Review Board (IRB) of the University of Vermont.

### Participants

Children from Malletts Bay School in grades 3rd, 4th, and 5th grade and ranging in age from 7 to 11 years will be recruited. An IRB approved consent form, group information form, as well as an introduction to the study letter will be sent home with each student. The letter will provide instructions as to how each interested student (along with a parent/legal guardian signature) should complete the consent form and group information form. Students will return their signed consent form along with a completed group information form to their teacher. Study staff will collect and review completed consent forms from the teachers.

Children will indicate on the group information form (included with the consent form) the group (A or B) they would like to participate (Table 1). The investigators will randomize the children to either Group A or Group B on a first-come, first-served basis. Once the maximum capacity for any one group (n = 50) is reached, children will be randomized to the other group if they have indicated their willingness to participate in the other group. Or if the preferred group is at maximum capacity and the child did not request to participate in the other group, then the child would be notified in writing that the requested group was no longer available.

**Table 1 T1:** Group Stratification

**Group A**	Week 0	Physical Activity Program	Week 12
	tests and measures	3 days/week	tests and measures
**Group B**	Week 0	No Physical Activity Program	Week 12
	tests and measures		tests and measures

Once the consent form is received by the study staff, children and parents will be notified through letters mailed to their home address as to what group their child will be participating. The parent(s) of the child will then be contacted by phone to schedule the first testing session.

For those in Group A, an approval from the child’s pediatrician to participate will be requested by the study staff. Parents will provide their child’s medical doctor information on the information form which will be turned in to the child’s teacher along with the signed consent form. Study staff will fax the medical clearance form specific to this study to the child’s doctor. The medical clearance form will include the child’s name, a description of the physical activity program, and a place for the doctor to provide/not provide their medical approval as well as any other medical recommendations. It is mandatory that we have their doctor’s written approval prior to their participation in the physical activity program. Study staff will notify the child’s parent by phone if attempts to obtain medical clearance from the child’s doctor are unsuccessful.

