### Assessments

All participant baseline measures will be performed 1–2 weeks prior to the first physical activity session. Follow-up measures will be performed within 1 week following the final physical activity session. For both Group A and Group B, the testing and measurement sessions will be scheduled at a convenient time before or after school and will be performed in a private room at the school. At the two testing and measurement visits, study staff will obtain weight, height, waist, hip and neck circumferences, resting heart rate and blood pressure for each enrolled child. Children will be asked to complete several questionnaires at both baseline and follow-up regarding their physical activity, eating habits, feelings and emotions, and quality of life. These measurements and questionnaires are expected to take approximately 15–20 minutes. Parent(s) will also be asked to complete questionnaires before and after the physical activity program. The parent questionnaires will include information regarding their education level, their child’s physical activity, eating habits, medications, illnesses, family history and quality of life. These questionnaires will be directly mailed to the parents and will include a postage-paid return envelope. We will also be asking teachers of enrolled participants to complete a brief questionnaire regarding the child’s classroom behavior before and after the physical activity program.

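### The form showing each child's group choice goes through the teachers, who rate classroom behavior and whose grades are an outcome; this exposure of likely raters is avoidable

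*Protocol article*

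**What the plan says.** All references are to the protocol article.

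- **The form shows the choice (Participants).** "Children will indicate on the group information form (included with the consent form) the group (A or B) they would like to participate".
- **The form goes to the teacher (Participants).** "Students will return their signed consent form along with a completed group information form to their teacher". The paragraph on medical clearance in the same section again has the information form handed in to the teacher. Study staff then collect the consent forms from the teachers.
- **The choice usually becomes the assignment (Participants).** Places go first-come, first-served. "Once the maximum capacity for any one group (n = 50) is reached, children will be randomized to the other group", and then only if they had said they were willing. Otherwise they are told that the requested group is no longer available.
- **Families learn the group before baseline testing (Participants).** After consent is received, "children and parents will be notified through letters mailed to their home address as to what group their child will be participating". Next comes: "The parent(s) of the child will then be contacted by phone to schedule the first testing session".
- **Teachers rate (Assessments).** "We will also be asking teachers of enrolled participants to complete a brief questionnaire" on classroom behavior, before and after the program. Under Academic performance, grades are listed with achievement test scores and two curriculum-based measures, M-COMP and Oral Fluency.
- **Children and parents report (Assessments).** "Children will be asked to complete several questionnaires at both baseline and follow-up", and parents receive mailed questionnaires before and after the program.

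**The concern.** Classroom behavior is a named objective, and its only described instrument is a teacher questionnaire. Grades also involve teacher judgement. A teacher who knows which children chose the activity program may, without meaning to, rate them more favorably afterwards, or rate them differently from the start. The article's procedure delivers that knowledge to the teacher before the program begins, although nothing in the design needs the teacher to have it.

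A second, smaller issue is the order of steps for children. Their Week 0 self-reports on activity, eating, emotions and quality of life come after the letter naming the group.

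The groups are self-selected, so the between-group comparison leans on Week 0 to account for baseline differences (Data analysis). A reporting shift linked to group can enter the direct Week 12 comparison. If it differs between Week 0 and Week 12, it also enters any baseline-adjusted comparison.

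**Working it through.** **Step 1: what each rater knows, and how firmly the article shows it.**

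| Rater | Outcome | Group information before the Week 0 report | Basis |
|---|---|---|---|
| Child | Activity, eating, emotions, quality of life | Own choice, then the group letter, then the testing session | Stated order in Participants |
| Parent | Mailed questionnaires | Own family's choice. The letter too, if the questionnaire comes after it | Choice stated; mailing date relative to the letter not given |
| Teacher | Classroom behavior; grades | Receives the form with the A/B choice | Receipt stated; reading it, being the same teacher who rates, and rating after the letters are inferred |

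**Step 2: choice versus assignment.** The two are the same until the preferred group reaches 50. After that, a child is either moved to the other group, having agreed to it, or not placed. For most enrolled children the form therefore shows the eventual group.

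**Step 3: where a reporting shift would appear.** Let b0 and b12 be the between-group reporting shift (A minus B, in SD units) at Week 0 and Week 12, with no true effect.

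- Independent t-test at Week 12 (planned in Data analysis): bias = b12.
- Difference in change from Week 0: bias = b12 − b0. If b0 = b12, it cancels. If they differ, it does not.
- Within-group change (offered in the Discussion as the answer to self-selection): the same raters supply both time points, so a group's change still carries any difference between their Week 12 and Week 0 reporting shifts.

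**Step 4: illustration of size.** The article gives no figure for such a shift, so there is none to reproduce. As a check of the method, its between-group sample size does reproduce: one-sided alpha 0.05, effect size 0.8 and power 0.8 give 20.03, so 21 per group and 42 in total.

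Inputs: n = 50 per group and alpha 0.05 (Data analysis); uncancelled shift b, assumed. The noncentrality is b × √(n/2) = b × √25 = 5b, with 2 × 50 − 2 = 98 degrees of freedom. For b = 0.2 it is 1.0, and for b = 0.3 it is 1.5. Rejection rates from the noncentral t distribution, with no true effect:

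| Assumed b (SD) | Two-sided 0.05 | One-sided 0.05 |
|---|---|---|
| 0 | 5.0% | 5.0% |
| 0.1 | 7.9% | 12.5% |
| 0.2 | 16.8% | 25.7% |
| 0.3 | 31.8% | 43.8% |
| 0.5 | 69.7% | 79.9% |

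The one-sided column is shown because the between-group power analysis uses a one-tailed test. The table describes one between-group comparison with a shift that does not cancel. It does not measure the effect of a contaminated Week 0.

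**The case against.** The strongest reply has five parts.

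1. **The teacher link is an inference.** The article does not say that teachers read the form, that forms are unsealed, that the receiving teacher is the rater, or that the first rating follows the letters. This stands, and it limits the point to likely raters. The routing itself is stated, however, and is not merely a detail left to a fuller document.
2. **Delaying the letters would hardly mask families.** They wrote the choice themselves. This stands. Only a baseline taken before the choice is made would do more, and Week 12 self-reports and parent reports cannot be masked at all.
3. **A clean Week 0 can remove a helpful cancellation.** If the shift were equal at both times, the change score would be unbiased. Cleaning only Week 0 would leave b12 in full. This is correct algebra, but it depends on an equality that nobody can check, and the Week 12 t-test gets no such benefit. It is a reason to limit what teachers know throughout, and not only at Week 0.
4. **Teachers may find out anyway.** Group A is active at school until 8:15 a.m. three mornings a week. This stands: the fix reduces exposure and cannot guarantee masking.
5. **The Discussion already admits self-selection.** It does, but it does not mention raters' knowledge of group, and its within-group remedy does not reach that (Step 3).

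A reader might also infer that disappointment distorts baseline or that children withdraw unequally before it. The article does not support this. No enrolled child is put in a group they did not accept, so disappointment could affect only those moved to a second choice, and nothing in the text bears on withdrawal. Nor does the article say that the academic conclusion rests on grades; they are one of several measures.

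**Conclusion.** The point holds in a limited form. The stated procedure passes the group choice through the teachers, who are the likely raters of classroom behavior and whose grades are one academic measure. That exposure is avoidable. For children, baseline self-report after the group letter follows from the stated order, but correcting it gains little because the choice is already known at home.

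A reader might go further and conclude that every subjective Week 0 outcome is reported with assignment known, so that baseline adjustment is spoiled. The article does not establish that. It is explicit for children only, inferred for teachers and undated for parents, and a constant shift would largely cancel in change scores.

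The size is not estimable from the article. The 17% and 32% figures rest on an assumed uncancelled shift of 0.2 or 0.3 SD, 50 per group, a two-sided 0.05 test and no true effect. This is an inexpensive improvement best made before recruitment, because what raters have learned cannot be undone in the analysis.

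**What to change.** 1. Have families return the group form in a sealed envelope or directly to study staff. Parent questionnaires already use postage-paid return envelopes.
2. Do not give teachers the group list, and obtain their Week 0 behavior ratings before groups are announced.
3. Where feasible, take child and parent baseline before the group letters, and ideally before the choice is made.
4. Score M-COMP and Oral Fluency under an ID code, and state that they take precedence over teacher grades for the academic conclusion.
5. Acknowledge that Week 12 child and parent reports are given with group known.

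**Cost.** Envelopes and a change in the order of existing steps. Some children would be measured and then get no place; how many depends on uptake, which the article does not give. Teachers may still learn the group from the children. If item 3 is impractical, items 1, 2 and 4 keep most of the benefit.

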## Discussion

The proposed study described in this paper is the first to the authors’ knowledge to examine the effect of an unstructured, moderate to vigorous, before-school physical activity program on academic performance, classroom behavior, emotions, and other health related measures in elementary school-aged children. The results of this study will provide evidence to support the feasibility and efficacy of an unstructured, moderate to vigorous, before-school physical activity program in children. The unstructured physical activity with limited equipment, yet moderate to vigorous intensity design would allow others to easily and affordably replicate. Often, the initiation of novel physical activity programs is often viewed as cost-prohibitive and labor intensive. The design, setting, and population, however, may be replicated in relatively any elementary school with limited supplies and with a limited budget. Furthermore, the proposed study will provide insight regarding the ideal physical activity intensity and duration necessary to achieve a positive increase in academic performance.

The current study allows the participants to select and/or indicate their preferred group- Group A, tests and measures with the physical activity intervention or Group B, tests and measures only. This randomization design may be considered a limitation of the study; however, differences within each group, treatment and control will be assessed in addition to comparisons between the two groups. These within-group analyses will allow evaluation of the outcomes attributable to the physical activity intervention rather than attitudinal variables that may have been introduced with the self-selection of the groups.

The findings of this study will provide valuable information for other research groups looking to increase physical activity levels of children via school-based interventions. Furthermore, it will ascertain whether an unstructured, moderate to vigorous, before-school physical activity program is an effective method for future large-scale implementation.

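### Allocation described as randomization is self-selection by preference and order of reply; the label, the main analysis and the effectiveness conclusion should be corrected to match

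*Protocol article*

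**What the plan says.** The allocation rule is in the protocol article under Methods/Design, Participants. Before assignment, "Children will indicate on the group information form (included with the consent form) the group (A or B) they would like to participate"; Table 1 shows that A is the program and B is no program. Then: "The investigators will randomize the children to either Group A or Group B on a first-come, first-served basis". When a group reaches 50, "children will be randomized to the other group if they have indicated their willingness to participate in the other group". A child who asked only for the full group is not placed: "the child would be notified in writing that the requested group was no longer available".

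The same section adds a step for Group A alone, namely the pediatrician's "written approval prior to their participation in the physical activity program".

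The Discussion acknowledges that participants choose their group and says: "This randomization design may be considered a limitation of the study". It then argues that analyses within each group will show what is attributable to the program and not to attitudes that come with self-selection. It closes by promising evidence of efficacy and a finding on whether the program is effective for wider roll-out.

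The Data analysis section plans independent t-tests between groups at Week 0 and Week 12, and a general linear mixed-model analysis of variance to account for baseline differences.

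**The concern.** Every allocation step is fixed by the family's stated preference, its speed in returning the form, or its willingness to switch. Serving families in order of arrival is a queue, not a random sequence. The article therefore describes one design and names another.

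The label matters because a reader, or someone pooling trials, will treat the A-versus-B difference as protected by chance assignment. It is not. Appetite for exercise, readiness to be at school by 7:30 and family engagement are all plausibly related to academic scores, behavior, mood, quality of life and body size. The raw Week 12 difference mixes these with the program effect.

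The remedy offered in the Discussion does not help. Pre-post change in Group A also contains 12 weeks of schooling, growth, familiarity with the tests and the motivation that led the child to choose A.

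**Working it through.** **1. Is there a chance element?** Taking the rule step by step:

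| Situation | What decides the group |
|---|---|
| Requested group has room | Child's preference |
| Requested group full, child willing to switch | Order of form return, plus willingness |
| Requested group full, child not willing | Child is not placed |

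No row contains a random draw.

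**2. The plan's own figure.** For the A-versus-B comparison the Data analysis section gives 21 per group (42 in total) from a one-tailed t-test, alpha 0.05, effect size 0.8, power 0.80. Power is P(T > t_crit), where T is noncentral t with 2n − 2 degrees of freedom and noncentrality d·√(n/2). With n = 21 the noncentrality is 0.8 × √10.5 = 2.59 and power is 0.817, so 21 per group reproduces. The calculation assumes that the groups differ only through the program, which this allocation does not secure.

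**3. The unadjusted Week 12 t-test under self-selection.** Input from the plan: n = 50 per group. Assumptions: no program effect, and a persistent advantage b (in SD units) for children who choose A. The article gives no value for b, so a range is shown. Noncentrality is b·√(50/2) = 5b; the two-sided critical value on 98 degrees of freedom is 1.984.

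| b (assumed) | Noncentrality | Rejects, two-sided | Rejects, one-sided |
|---|---|---|---|
| 0 | 0 | 5.0% | 5.0% |
| 0.2 | 1.0 | 16.8% | 25.7% |
| 0.3 | 1.5 | 31.8% | 43.8% |
| 0.5 | 2.5 | 69.7% | 79.9% |

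The one-sided column is shown because the between-group power analysis is one-tailed.

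**4. The planned mixed model in the same scenario.** Two readings are possible, since the article does not say how baseline enters.

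- *Group-by-time term.* With two time points this is the comparison of change scores. A persistent b cancels: (b at Week 12) − (b at Week 0) = 0.
- *Baseline as covariate.* With pre-post correlation r, the bias left over is b(1 − r) and the residual SD is √(1 − r²). For b = 0.5 and r = 0.7 the bias is 0.15 against a residual SD of 0.71; for r = 0.8 it is 0.10 against 0.60.

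Simulation (20,000 trials per setting, 50 per group, two-sided, r assumed):

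| b | Group-by-time | Covariate, r = 0.7 | Covariate, r = 0.8 |
|---|---|---|---|
| 0.2 | about 5% | 7% | 6% |
| 0.3 | about 5% | 9% | 8% |
| 0.5 | about 5% | 17% | 12% |

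**5. What adjustment leaves.** Let τ be the program effect, and m_A and m_B the changes the two groups would have shown over 12 weeks without the program. The group-by-time contrast estimates τ + (m_A − m_B). Random assignment makes the bracket zero on average; self-selection does not. Covariate adjustment handles only the part of the difference that the measured baseline carries. The article gives nothing from which m_A − m_B could be sized.

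**6. The within-group defence.** A pre-post test in Group A estimates τ + m_A. With τ = 0, n = 50 and an assumed ordinary gain of g SDs of change, the noncentrality is g·√50. For g = 0.3 (2.12) the two-sided test rejects in about 55% of studies; for g = 0.5 (3.54), in about 93%. A significant within-group change is thus expected even if the program does nothing.

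**The case against.** The strongest reply is that the article discloses self-selection and plans a model for baseline differences. In the scenario of a stable baseline gap, that model does what it should: the inflation falls to about 5%, or to 6–17%. The Week 0 t-test would also flag a 0.5 SD gap in about 70% of studies. All of this stands, so the 17%, 32% and 70% belong to the unadjusted Week 12 t-test only and are not error rates for the plan as a whole.

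A concurrent non-randomised comparison is also a legitimate choice for a one-school program. A reader might infer that the A-versus-B comparison is worthless; the documents do not support that. An adjusted and openly non-randomised comparison remains informative. The error lies in the label and in the strength of the conclusion.

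A reader might also infer that medical clearance biases Group A. The article makes clearance a condition of taking part in the program, but it does not say that uncleared children leave the study or the analysis, and it gives no refusal rate. That is an open question of handling, not a demonstrated bias.

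The reply does not rescue the wording. Disclosure is attached to a design still called randomized, and the safeguard offered with it, the within-group analyses, does not separate program from selection.

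**Conclusion.** The point holds. The Participants section describes preference-based, first-come allocation and calls it randomization. The Discussion repeats the term while conceding self-selection, and draws an effectiveness conclusion that the design cannot carry in that form.

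The numerical size depends on the analysis. On the assumed advantages of 0.2 to 0.5 SD with no program effect, the unadjusted two-sided Week 12 t-test is wrong in about 17% to 70% of trials, and the planned mixed model in about 5% to 17% depending on its form. The shifts and the correlations of 0.7 and 0.8 are assumptions. Bias from differing trajectories or unmeasured motivation remains under either form and cannot be quantified from the article.

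**What to change.** 1. In Participants and Discussion, delete *randomize*, *randomized* and *randomization design*. Describe a non-randomised, preference-based controlled study with places filled in order of reply.
2. In Data analysis, make the baseline-adjusted between-group comparison the main analysis in place of the unadjusted Week 12 t-test, and state whether baseline enters through the group-by-time term or as a covariate.
3. In the Discussion, delete the claim that within-group analyses isolate the program effect, and replace the efficacy and effectiveness wording with a conclusion about an adjusted, non-randomised association.
4. State that children stay in their assigned group for analysis when Group A clearance is not obtained.

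Items 1 to 4 cost wording and one analysis decision; recruitment does not change.

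An optional redesign is to assign the children willing to enter either group from a concealed random list and to analyse single-preference children separately. The allocation rule already depends on that willingness being recorded. This is not a wording change: it alters what families are offered under the approved consent and group form, so it needs renewed ethics approval. The number of such children is unknown and could fall below the 42 that the plan's own power calculation requires, so it should be checked first.
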